### Quality of life assessment

Brain cancer severely affects patients’ QoL, which is to a great extent caused by cognitive dysfunction and personality changes due to treatment or the disease itself [4, 41, 42]. Here it is hypothesized that patients’ health-related QoL (HRQoL) will decrease less in the HA-WBRT+SIB group than in the WBRT+SIB group.

HRQoL is assessed by the European Organisation for Research and Treatment of Cancer (EORTC) Quality of Life Core Questionnaire for Palliative Care (QLQ-C15-PAL) [43], as well as the brain cancer-specific module QLQ-BN20 [44], which addresses symptoms that are specific to brain cancer and its treatment [45]. The QLQ-C15-PAL includes those domains and symptoms of the parent instrument, QLQ-C30 [46], identified as most relevant and important for palliative care, namely physical (two items) and emotional functioning (two items), the symptom scales fatigue (two items), and pain (two items), as well as five single items (dyspnea, insomnia, appetite loss, nausea, and constipation), and the global quality-of-life index [43]. This abbreviated questionnaire has shown better compliance and practicability compared to the QLQ-C30 [42]. The additional brain cancer-specific module QLQ-BN20 comprises eleven scales, among them four multi-item scales addressing future uncertainty (four items), visual disorder (three items), motor dysfunction (three items), and communication deficits (three items). The additional seven single-item scales assess headaches, seizures, drowsiness, hair loss, itchy skin, weakness of legs, and bladder control. The construct validity of the QLQ-BN20 has been tested and confirmed with regards to the EORTC QLQ-C30 [44] and it has shown a good reliability, with acceptable responsiveness to changes over time [45].

Symptom control and physical functioning is only one dimension of QoL and patients have their own coping resources to deal with their disease and therapy side effects. One of the best established instruments to evaluate Individual QoL (IQoL) is the Schedule for the Evaluation of Individual Quality of Life – Direct Weighting (SEIQoL-DW), an abbreviated form of the SEIQoL [47]. This highly valuable instrument asks about the satisfaction of the patients with different domains of life (e.g. family, work or health) and weights the results considering the individual relative importance of these domains for the patient. The SEIQoL-DW has been proven to be a valid and reliable measure of IQoL also in terminally ill patients. In our study the nomothetic measurement of HRQoL is complemented by the SEIQoL-Questionnaire (SEIQoL-Q) [48], developed to transform the interview guide of the original SEIQoL-DW into an economic written self-report that can be easily implemented in a high-volume radiotherapy unit.

The SEIQoL-Q is applied parallel to QLQ-C15-PAL and -BN20 before treatment and 3, 9, and 18 months after treatment. Beyond 18 months after the end of WBRT, all patients who are still alive receive HRQoL assessment with the SEIQoL-Q questionnaire once per year.

### Magnetic resonance imaging (MRI)

In this trial we also aim to investigate the putative benefit of HA-WBRT+SIB with state-of-the-art MRI methods. It is assumed that differential treatment effects will be detectable mainly within the hippocampus, in terms of volume change, reflecting effects on NCF. Therefore, hippocampal volume is measured at baseline and at follow-ups, in order to evaluate and compare changes between treatment groups. Similarly, brain volume changes after treatment are compared in order to detect brain atrophy.

Moreover, it is hypothesized that white matter toxicity (leukoencephalopathy) will be detectable initially in both treatment groups. We further hypothesize that patients receiving HA-WBRT+SIB will show a better recovery of lesions compared to patients receiving treatment without HA. It is assumed that this effect will arise from the sparing of the neural progenitor cells in the subgranular zone of the dentate gyrus of the hippocampus during HA-WBRT+SIB. Sparing of neural progenitor cells might hence allow for a better regeneration in terms of gliogenesis of white matter oligodendroglial cell populations.

Diffusion Tensor Imaging (DTI) studies in neurodegenerative diseases suggested that changes to the hippocampus are also associated with structural changes of the hippocampus output fibres. In patients with Alzheimer’s disease and Lewy Body Dementia, changes of the hippocampus correlated with decreased fractional anisotropy in the fornix and stria terminalis [49]. Decreased fractional anisotropy within outgoing fibres was discussed to be a result of Wallerian degeneration, with primary degeneration of hippocampal neurons leading to loss of output fibres. In another study increased diffusivity parameters were found in parahippocampal gyrus, posterior cingulum, adjacent temporo-parietal regions, splenium and fornix of patients with Alzheimer’s disease compared to age-matched healthy controls [50]. In children treated for acute lymphoblastic leukemia, DTI has previously been used to characterize neurotoxicity [51], with reduced fractional anisotropy after irradiation being associated with impaired neuropsychological test performance. Consequently, an extensive study-specific MRI protocol is planned for all follow-ups, including the following sequences: 3D fluid-attenuated inversion recovery (FLAIR), diffusion-weighted MRI (DWI), DTI, diffusion kurtosis imaging (DKI), T2 and T2* relaxometry, and a 3D T1-weighted, gradient-echo sequence (MP RAGE) before and after contrast agent injection.

### Local tumor control (LTC) and occurrence of new cerebral metastases

In order to ensure comparable efficacy of HA-WBRT+SIB and conventional WBRT+SIB, LTC and the occurrence of new cerebral metastases will be continuously monitored, especially within the hippocampal area. Study-specific MRI will be performed at baseline and 6 weeks, 3, 9, and 18 months after treatment. Clinical routine MRI will be performed 6 and 12 months after treatment. Beyond 18 months after the end of radiotherapy, documentation of progression based on clinical routine MRI is performed once per year for all patients who are still alive.

Time to progression is defined as the number of days from randomization to the first occurrence of the respective event. The date of occurrence is the first date on which progressive disease was suspected, if subsequently confirmed according to the study procedures.

Intracranial progression is defined as the occurrence of progressive disease (at least 20% increase in the sum of the longest diameter of the contrast enhancing lesion) concerning pre-existing brain metastases or the occurrence of new brain metastases [52]. Tumor progression in the area of dose escalation has to be distinguished from treatment-related changes. Progressive lesions can initially be treated conservatively for 6 weeks with dexamethasone (e.g. 3 × 4 mg/d for 4 days followed by a 2-mg dose reduction every 2 days) and pentoxifylline (400 mg twice a day). After 6 weeks, a control MRI scan is to be performed. If no further progression is noted, treatment-related changes are diagnosed and follow-up is continued. If a further increase in the contrast-enhancing lesions is seen, an intervention is initiated after interdisciplinary discussion, including surgery or biopsy – if medically and ethically indicated. Histological evidence of necrosis without vital tumor cells in a biopsy or resection leads to the diagnosis of radiation necrosis, whereas histological evidence of tumor or the initiation of further therapy leads to the diagnosis of local tumor progression.

Progression in the WBRT area without dose escalation is defined as occurrence of intracranial tumor progression (progression of existing lesions and/or occurrence of new lesions) in the WBRT area without dose escalation. Hippocampal progression is defined as occurrence of intracranial progression within the hippocampal avoidance region (HAR, hippocampus + 7 mm). For patients not diagnosed with the respective event at the end of the study, the respective time to progression will be censored at the time of the last available imaging assessment. Death before the occurrence of the respective progression is considered a competing event.

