### Statistical planning and analysis

The sample size calculation is based on the primary outcome, which is defined as the difference between the learning scale of the VLMT (word count, 0–75 words) in survivors at 3 months after radiation therapy and at baseline.

Assuming a mean decline after WBRT+SIB of 15 words in VLMT and a common standard deviation of 15 words [6], the study is planned to reject the null-hypothesis of equality of treatment arms with 80% power on the basis of a two-sample t-test at a one-sided significance level of 10% if the deterioration of NCF improves to a 7 words decline after HA-WBRT+SIB. Under these assumptions, 66 patients are required for analysis. According to the patients’ prognosis, we expect about 55% of patients in both arms to survive until 3 months after radiation, plus some additional drop-out of patients unwilling or unable to perform the test. We reckon that 50% of randomized patients will be available for analysis. Therefore, 132 patients should be randomized.

In the primary analysis, differences between HA-WBRT+SIB and WBRT+SIB with respect to the primary endpoint will be estimated and tested within a linear regression model in patients who survive until 3 months after radiation therapy. The model will include treatment and study center as independent variables and will adjust for the baseline learning scale word count of the VLMT. In case of endpoint values missing for reasons other than patient death, these will be handled by multiple imputation. The primary analysis population is the per-protocol set, defined as the group of randomized patients who had no major violations of eligibility criteria and who received treatment as per protocol according to their randomized arm. Sensitivity analyses of the primary endpoint as pre-defined in the study protocol will be performed.

Descriptive and explorative statistical analyses will be performed with respect to the secondary efficacy endpoints. Overall, PFS rates in the two treatment arms will be estimated by the Kaplan-Meier method, and the corresponding endpoints will be analyzed with the Cox model.

For safety analyses, rates of adverse events and the use of corticosteroids will be calculated with 95% confidence intervals.

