## Discussion

The optimal treatment of multiple brain metastases has been the subject of increased controversy in the last decade and is a research question of great epidemiologic impact. While technical advances now allow the synchronous radiosurgical treatment of as many as 10 brain metastases [54, 55], insuring intracranial distant tumor control still remains imperative. Thus, despite known long-term side effects, WBRT is still the standard therapy for multiple (≥4) brain metastases [2, 3].

Approaches to improve the risk-benefit ratio for WBRT have been manifold. One of them was the sequential application of radiosurgeries to the metastases, used to increase the otherwise modest LTC [26]. In this case, the choice of a simultaneous boost application in the HIPPORAD-trial has the biological advantage of fractionation and ensures a better sparing of the hippocampi [27]. The tumor control and survival achieved in this trial will be compared with published data on WBRT alone and WBRT with sequential radiosurgeries to the metastases [24, 26, 53].

Another approach to preserve the integrity of cognitive functions involved the prescription of lower doses to the whole brain. While these appear to limit long-term adverse events such as atrophy and leukoencephalopathy, very low doses or no WBRT at all have also proved ineffective in insuring intracranial tumor control [3, 56]. The dose chosen in our trial for the CTV_WB_ (30 Gy/2.5 Gy) is only moderately lower than the standard 30 Gy in 10 fractions (with an equivalent dose in 2 Gy fractions, EQD2, α/ß = 10 of 32.5 Gy, a biological effective dose, BED, of 39 Gy and an EQD2 α/ß = 2 of 37.5 Gy). The dose applied in the HIPPORAD trial corresponds to an EQD2 α/ß = 10 of 31.25 Gy, BED 37.5 Gy and an EQD2 α/ß = 2 of 33.75 Gy. This slight de-escalation takes into consideration the smaller prescription volume (PTV_WB_ – PTV_met_ – HAR) and the allowed multiple boosts. Whether this approach will prevent whole brain atrophy and cognitive side effects, but come with the trade-off of poorer distant tumor control, as seen previously [22], has to be prospectively analyzed in this trial.

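### In the boosted area, a suspected local progression that death or loss leaves unconfirmed is not counted and may be censored at the suspicious scan, which probably understates local progression modestly

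*Protocol article*

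**What the plan says.** The rules are in the protocol article, in the section on local tumor control and new cerebral metastases and in the section on PFS and OS.

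- **Event definition.** "The date of occurrence is the first date on which progressive disease was suspected, if subsequently confirmed according to the study procedures".
- **Confirmation in the boosted area.** "Tumor progression in the area of dose escalation has to be distinguished from treatment-related changes". To that end, "Progressive lesions can initially be treated conservatively for 6 weeks with dexamethasone" and pentoxifylline. "After 6 weeks, a control MRI scan is to be performed". If there is no further growth, treatment-related change is diagnosed. If there is further growth, an intervention follows, and tumor on histology or the start of further therapy establishes local progression.
- **Death, time-to-progression endpoints.** "Death before the occurrence of the respective progression is considered a competing event".
- **Death, PFS and local PFS.** Death without prior progression is an event.
- **No diagnosed event, time to progression.** The time "will be censored at the time of the last available imaging assessment". Local PFS uses the same rule for patients who are alive.
- **No diagnosed event, PFS.** The rule is different: the patient is censored when freedom from intracranial progression (on imaging) and from extracranial progression was last established.

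Two further statements bear on the size and use of these endpoints. Under statistical planning, "we expect about 55% of patients in both arms to survive until 3 months after radiation". In the Discussion, "The tumor control and survival achieved in this trial will be compared with published data on WBRT alone", and also with data on WBRT followed by radiosurgery.

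**The concern.** Each rule is reasonable alone; the difficulty lies in their combination. Take a patient whose boosted lesion meets the 20% growth criterion and who never reaches confirmation. Whether that growth counts as local progression then depends on whether the patient stays alive, fit and in follow-up long enough to be rescanned, biopsied or treated further. Patients in poor condition are the least likely to get there.

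Censoring at the last available scan makes this worse for patients lost alive. If that scan raised the suspicion, the patient leaves the risk set on the very day progression was suspected, and the analysis treats the patient as having the same future risk as those with a clean scan.

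Local control is part of the trial's main hypothesis, and the Discussion plans to set the absolute tumor control beside published results. Randomization does not protect that external comparison, even if the effect is equal in both arms.

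**Working it through.** **Reproducing the plan's figures.** The article gives no expected value for any progression endpoint. Its only sized endpoint is the VLMT change: difference 8 words, SD 15, one-sided 10%. By the noncentral t distribution, 33 per arm gives power 0.808 and 32 per arm gives 0.799, so 66 analyzable patients is right, and 66/0.5 = 132 randomized. Nothing below touches those numbers.

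**Outcome of an unconfirmed suspicion under the stated rules**

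| What happens before confirmation | Time to local progression | Local PFS | PFS |
|---|---|---|---|
| Patient dies | Competing event | Event at death, not at suspicion | Event at death, not at suspicion |
| Patient lost alive | Censored at last scan, possibly the suspicious one | Same | Censored when last known free of progression, most naturally before the suspicion |

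The two columns for patients lost alive show that the article applies two censoring principles to the same situation.

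**Chance of dying during the wait.** Inputs: survival S to 3 months (91.3 days) of 0.55, from the article; wait of 42 days, from the article; constant hazard, assumed.

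P(death within 42 days) = 1 − S^(42/91.3) = 1 − 0.55^0.460 = 0.240.

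If the 55% is taken to apply from about 16 days earlier, to allow for the radiotherapy course, the exponent is 42/107.3 and the result is 0.209.

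**Effect on 12-month cumulative incidence.** Let h = −ln(S)/91.3 be the daily death hazard and l = −ln(1 − p)/365 the daily local progression hazard, where p is an assumed net 12-month risk. Then:

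- True incidence = l/(l + h) × [1 − exp(−(l + h) × 365)]
- Counted incidence = true incidence × exp(−42h)

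Example with S = 0.55 and p = 0.20: h = 0.00655, l = 0.000611. True = 0.0854 × 0.927 = 0.079. Counted = 0.079 × 0.760 = 0.060.

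| 3-month survival | Death in 42 days | Assumed net risk | True | Counted | Difference (points) |
|---|---|---|---|---|---|
| 55% (article) | 24.0% | 10% | 3.9% | 2.9% | 0.9 |
| | | 20% | 7.9% | 6.0% | 1.9 |
| | | 30% | 12.2% | 9.2% | 2.9 |
| 70% (assumed) | 15.1% | 10% | 5.4% | 4.6% | 0.8 |
| | | 20% | 10.9% | 9.3% | 1.7 |
| | | 30% | 16.6% | 14.1% | 2.5 |
| 80% (assumed) | 9.8% | 10% | 6.7% | 6.0% | 0.7 |
| | | 20% | 13.4% | 12.1% | 1.3 |
| | | 30% | 20.4% | 18.4% | 2.0 |

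Differences are taken before rounding. The calculation assumes that every local progression passes through the 6-week wait, that every suspicion is true, and that no other route confirms it; these push the figure up. It also assumes that progression does not raise the death hazard and leaves out patients lost alive; these push it down. The higher-survival rows are there because a constant hazard from 55% implies only about 0.55^4 = 9% alive at 12 months.

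**The case against.** The case on the other side is substantial.

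- **Deaths are not ignored.** A reader might infer that patients who die unconfirmed are counted as progression-free. They are not. They are events in PFS and local PFS, where only the date moves (by at most about 6 weeks for a death within the wait), and competing events in time to progression. Patients lost alive are censored, not carried forward as controlled. This stands.
- **The wait is neither general nor compulsory.** The wording is permissive, and the step is described for the dose-escalated area. Nothing requires it for new metastases, unboosted lesions or extracranial progression, so the 6-week argument does not extend to intracranial progression as a whole. This stands.
- **Other routes exist.** Histology, the start of further therapy or a later scheduled scan can still establish progression. This stands as a limit on size, although patients too ill for the control scan are also less likely to reach these.
- **Confirmation has a purpose.** Some growth after a boost is treatment-related, so counting every suspicion would err the other way. Dating back to first suspicion also avoids delay in confirmed cases. This stands.
- **The full protocol may settle it.** The article refers to study procedures that are not shown, and these endpoints are secondary and descriptive. Silence alone would not be a finding. But the article's stated rules already produce a result for these patients, and the censoring rule for local endpoints is at odds with its own PFS rule.

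**Conclusion.** For boosted lesions the stated rules leave out suspected local progressions that cannot be confirmed, and they permit censoring on the day of suspicion. This probably understates local progression modestly. The probability of death within the wait is 21% to 24% under the protocol's survival figure and a constant hazard. The loss of roughly 1 to 3 points of 12-month incidence rests on assumed progression risks of 10% to 30% and on the simplifications listed in the check.

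Two stronger readings are not supported. First, a reader might take one quarter off an incidence of 20% and conclude that 4 to 5 points are lost, or more if the death hazard doubles after progression. The documents give neither a 20% incidence nor a doubled hazard. With 55% three-month survival held constant, a net risk of 20% yields a true incidence of only 7.9%, because most patients die first. Second, a reader might infer a bias between the arms. Both arms receive the boost, follow the same rule and have the same expected survival, so none is shown.

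The direction is likely but not certain, since the share of suspicions that are treatment-related is unknown. How far the comparison with published data is affected also depends on how those studies confirmed progression, which the documents do not say.

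**What to change.** Change the endpoint and analysis wording only; no change to clinical management is proposed.

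1. For time to progression and local PFS, censor living patients with an unresolved suspicion at the last scan that showed no suspected progression, in line with the existing PFS rule. This removes censoring on the day of suspicion but not all informativeness, hence the second step.
2. State how a suspicion is classified when death, deterioration or withdrawal prevents confirmation. Report local progression and local PFS both ways: counted as progression at the date of first suspicion, and confirmed only. Show both wherever tumor control is compared with published data.

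The cost is small. No extra scans are needed, provided that the date of each suspicion is recorded even when it is never confirmed. The one downside is that the first version will count some treatment-related changes as progression, so reported tumor control will look slightly less favourable; the confirmed-only version shows the other end of the range.

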### Progression-free survival (PFS), overall survival (OS) and death caused by cerebral metastases

PFS will be calculated from randomization until the first occurrence of intracranial or extracranial progression, death without prior progression, or end of follow-up. For patients alive and not diagnosed with progression at the end of the study, the PFS time will be censored at the time the patient was last known to be free of intracranial progression based on imaging assessment and free of extracranial progression. Local PFS is defined as the number of days from randomization until local tumor progression, death without prior local progression, or end of follow-up. Patients alive and not diagnosed with local progression at the end of the study will be censored at the time of the last available imaging assessment.

OS will be calculated from randomization until death, and time to death caused by cerebral metastases will be calculated from randomization to death if caused by cerebral metastases. For patients alive the end of the study, OS will be censored at the time of the last follow-up. For the time to death caused by cerebral metastases, death from other causes is considered a competing event. Death due to cerebral metastases is defined as intracranial failure as a component of cause of death [53].

The time to extracranial progression will also be calculated from randomization until extracranial progression or end of follow-up, where extracranial progression is the first date on which progressive disease outside the brain occurred. For patients alive and not diagnosed with extracranial progression at the end of the study, the time to extracranial progression will be censored at the time the patient was last known to be free of extracranial progression. Death before the occurrence of extracranial progression is considered a competing event.

The application of systemic therapies prior or subsequent to irradiation is to be thoroughly documented throughout the study.

